### Power analysis and sample size

Evidence from our recent meta-analysis of cognitive training for adults with hearing loss reported beneficial effects ranging from small to large [17], with contributing studies including 10 to 67 participants. Using G*Power (34), an a priori power analysis was conducted to determine the required sample size when comparing two intervention groups across three measurement intervals (i.e. pre-intervention, post-intervention, and 3-month follow-up) for any of the primary outcome measures (speech/sound perception or cognition). To detect a medium effect (*f*
^2^ = .25) at an alpha of .05 and power of .90, 36 participants will need to be recruited. To account for potential 20% attrition, 44 participants (i.e. 22 per group) will be targeted for recruitment.

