### Outcome measures

The primary outcome measures will be cognitive functioning and speech/sound perception as described below. The secondary outcome measures will be mood and quality of life as described below. All outcome measures will be measured as discrete or continuous data.

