#### Cognition

In accordance with the Cattell-Horn-Carrol-Miyake (CHC-M) taxonomy of cognitive outcomes [20], a battery of non-verbal neuropsychological tests will be used to measure broad ability domains of general short-term memory (Gsm) and executive function (EF). Six tests will be used to measure each narrow ability domain within the broad domains of Gsm and EF.

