#### Sound and speech perception

A standardised pure-tone audiometric assessment (Equinox 2.0 clinical audiometer) will be used to assess participant pure-tone average (PTA) hearing thresholds across octave frequencies between 0.25 and 8 kHz. In accordance with clinical guidelines for cochlear implantation [18], speech perception will be assessed using an open-set list of 25 monosyllabic words (consonant-vowel-consonant [CVC] words [25]) scored as the percentage of phonemes and words correct. Speech perception will also be assessed using the open-set City University of New York (CUNY) sentences [26] and scored as percentage correct. Pre-implantation speech perception will be delivered via optimised hearing aids in quiet, with words and sentences assessed up to 65 dB through unilateral and bilateral hearing aids. Post-implantation speech perception assessments will be conducted using the speech processor.

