### Data analysis and statistical methods

SPSS (version 26) will be used to calculate descriptive statistics for demographic data and outcome test results at pre-intervention, post-intervention, and 3-month follow-up assessments. Generalised linear mixed models (GLMMs) will be used to analyse outcome variables. Each GLMM will be assessed for statistically significant Group x Time interaction effects, main effects of Time (per group), and pairwise contrasts. Age effects on cognitive training will be considered in the statistical analysis and results will be discussed accordingly.

Following a wave of recent criticism drawing attention to the limitations of the frequentist approach (i.e. *p* values and alpha levels) of statistical analysis, there has been increasing recommendations for researchers to report Bayes factors to support the interpretation of their findings [33]. Within the frequentist approach, it is most frequently misunderstood that a statistically significant *p* value (i.e. *p* ≤ .05) provides evidence in support of an alternative hypothesis, whereas a statistically significant *p* value can only provide evidence to disprove the null hypothesis and cannot suggest whether the observed data supports an alternative hypothesis [33]. Compared to the frequentist approach, however, the Bayesian framework allows researchers to quantify whether changes in their observed data favour the null hypothesis or their alternative hypothesis by considering prior odds (i.e. prior evidence of similar effects). It is therefore important that researchers report Bayes Factors alongside frequentist statistics to provide a more informative interpretation of their findings. From the GLMM results, Bayes Factors will be approximated using the Bayesian Information Criterion (BIC) from each model (i.e. H0 and H1) and reported to provide evidence of whether auditory training combined with adaptive CCT improves study outcomes to a greater extent, when compared to auditory training combined with non-adaptive (i.e. placebo) CCT.

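### About ten unranked primary scores are each assessed for significance while the sample size uses one unadjusted alpha of .05, so the primary false-positive rate is uncontrolled and the stated .90 power holds only per outcome

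*Protocol article*

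**What the plan says.** The Outcome measures section of the protocol article sets the primary set by domain: "The primary outcome measures will be cognitive functioning and speech/sound perception as described below".

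- **Cognition.** "Six tests will be used to measure each narrow ability domain within the broad domains of Gsm and EF". The tests are LNS, PAL, DMS, spatial N-back, TMT-BA and MTT, each with its own subsection. No composite is defined.
- **Sound perception.** Pure-tone audiometry "will be used to assess participant pure-tone average (PTA) hearing thresholds across octave frequencies between 0.25 and 8 kHz".
- **Speech perception.** CVC words are "scored as the percentage of phonemes and words correct", which gives two scores. For sentences, "Speech perception will also be assessed using the open-set City University of New York (CUNY) sentences [26] and scored as percentage correct".

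That is 6 + 1 + 2 + 1 = 10 primary scores. The article does not order them, name a deciding one, or say how many must succeed.

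Data analysis and statistical methods plans mixed models for the outcome variables: "Each GLMM will be assessed for statistically significant Group x Time interaction effects, main effects of Time (per group), and pairwise contrasts". BIC-based Bayes factors are to be reported next to the p values.

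Power analysis and sample size describes a calculation for two groups and three assessments "for any of the primary outcome measures (speech/sound perception or cognition". It concludes that "at an alpha of .05 and power of .90, 36 participants will need to be recruited". The recruitment target, with attrition, is 44.

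**The concern.** When ten scores are all primary and each is examined for significance, a chance finding on at least one of them is far more likely than 5%. The sample size calculation treats the trial as if there were a single primary test. Two things are at stake:

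- **False positives.** A significant interaction on one of ten scores could be reported as a primary result in favour of adaptive training, although such a result would arise in a substantial share of trials of an ineffective programme.
- **Power.** If the error is controlled, the power is no longer the stated .90. As N is fixed at the full alpha, the article can keep either the error rate or the stated power, but not both.

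**Working it through.** **1. Reproduce the plan's figure.** Inputs from the article: k = 2 groups, m = 3 assessments, alpha .05, power .90, effect size .25. Not stated and therefore assumed: repeated-measures correlation rho = .5 and sphericity. For the within-between interaction:

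- lambda = f² × N × m / (1 − rho) = .0625 × 36 × 3 / .5 = 13.5
- df1 = (k − 1)(m − 1) = 2; df2 = (N − k)(m − 1) = 68
- critical F at .05 = 3.13; power = .906

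N = 34 gives .888, so 36 is the smallest even N that reaches .90. The figure therefore reproduces with the full alpha of .05 and contains no allowance for multiple outcomes. (The article prints the effect size as f squared. Read literally, f = .5, N would be 12; only f = .25 gives 36. That is a separate point.)

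**2. Chance of at least one significant primary interaction when nothing works.** One 2-df interaction test per score, each at .05:

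- Ten independent scores: 1 − .95^10 = .401
- Six cognitive tests alone, independent: 1 − .95^6 = .265

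The article gives no between-outcome correlations, so a range was simulated (ten equally correlated outcomes, 18 per group, 2-df F test):

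| Assumed correlation | At least one significant |
|---|---|
| 0 | 40% |
| .3 | about 35% |
| .5 | about 29% |
| .7 | about 22% |

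A block structure (.3 within cognition, .7 within speech/sound, .1 across) gives 35%. These figures count the interaction tests only.

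**3. Power once alpha is adjusted.** Same formula, f = .25, rho = .5:

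| Adjustment | Alpha per test | Power, N = 36 | Power, N = 44 | Evaluable N for .90 |
|---|---|---|---|---|
| None | .05 | .906 | not computed | 36 |
| Split over two domains | .05/2 = .025 | .847 | .921 | 42 |
| Bonferroni over ten | .05/10 = .005 | .665 | .794 | 56 |

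The N = 44 column supposes that nobody drops out. Fifty-six evaluable at 20% attrition means 56/.8 = 70 recruited. Bonferroni is the lower bound on power; Holm loses somewhat less.

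**4. Power of a composite, if one were chosen.** Suppose each of the six tests differs by 0.5 SD and they correlate .3. The SD of their mean is sqrt((1 + 5 × .3)/6) = .645, so the composite differs by .5/.645 = 0.77 SD. For a baseline-adjusted contrast at the post-intervention assessment (T1), with 18 per arm and baseline correlation .5, the noncentrality is 0.77/sqrt(1 − .25) × sqrt(18/2) = 2.67. Power is about .74 at alpha .05 and about .63 at .025. The .847 in step 3 belongs to the three-assessment interaction and does not carry over to this contrast.

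**The case against.** **The article states no win-on-any rule.** A reader might infer that one significant score makes the trial positive, or that the outcome and time point will be chosen after the data are seen. The text does not support that. The word "any" in the power section says which measures the calculation covers, and no success rule of any kind is given. This objection stands. The familywise figure does not depend on such a rule, however: it is the chance that at least one primary interaction is significant.

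**No test level is stated for the models, and multiplicity procedures are often left to an analysis plan.** Both are true: the only planned .05 is in the power calculation, and a separate plan may exist. The absence of an adjustment is therefore not the point. The article itself fixes an unranked primary set and sets N at the full alpha. If an adjustment across the ten is made elsewhere, the .90 stated here does not hold; if none is made, the error is uncontrolled.

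**Bayes factors offer protection.** In part. For a 2-df interaction, the large-sample BIC approximation gives BF01 = n × p. At p = .05 this favours the null by 36 × .05 = 1.8, or by 108 × .05 = 5.4 if n counts observations. A borderline p value would thus appear beside a Bayes factor against the effect. Requiring BF10 above 3 (an assumed threshold) would bring the chance over ten independent tests to about 9% (n = 36) or 3% (n = 108); requiring only BF10 above 1 at n = 36 leaves 25%. The article sets no threshold, so this mitigates the problem without controlling it.

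**The problem can be overstated.** One might count every Time effect and pairwise contrast and arrive at some 120 tests. Many of those are within-group or baseline comparisons, which do not test adaptive against non-adaptive training. Nor is one hit in ten close to what chance predicts: the expected number is 10 × .05 = 0.5, and no hit is the likelier result.

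**Conclusion.** The concern holds in this form: about ten scores are primary with no ranking, composite or success rule, each model is assessed for significance, and N is set at one unadjusted alpha of .05. The chance of at least one significant primary interaction under a complete null is 40% for independent scores and about 22% even at a correlation of .7, against a nominal 5%. The stated .90 power is correct for a single outcome without adjustment; at N = 36 it becomes about .85 (two domains) or about .67 (Bonferroni over ten).

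The error figures rest on testing each interaction at .05 and on assumed between-outcome correlations. The power figures rest on f = .25 and an assumed repeated-measures correlation of .5. The direction of both conclusions does not depend on the exact values.

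**What to change.** The Trial status section says that recruitment had not begun, so the change can be made before any data exist. Choose one of two routes:

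1. Keep all ten scores primary and apply Holm across the ten Group x Time interaction tests.
2. Name one cognitive score and one speech score as primary, apply Holm across the two, and make the other scores secondary.

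Under either route, treat within-group Time effects and pairwise contrasts as descriptive, and restate the power in Power analysis and sample size at the adjusted level.

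A cognitive composite is an option, not a requirement. It would need signs aligned, since a higher LNS score is better while a larger TMT-BA difference is worse. If a T1 composite contrast becomes primary, its own power must be stated: about .74 at .05 or .63 at .025 under the assumptions in the working.

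The cost is rewording of the protocol and registry entry, a stricter threshold, and a lower stated power at the planned N. Keeping .90 would need about 42 evaluable participants for two primaries (at .025), or 56 for ten under Bonferroni (fewer under Holm where several outcomes respond).

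### The planning effect is printed as f² = .25, but the stated 36 participants fit f = .25, which is a group difference of about 1.06 SD and not a moderate one

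*Protocol article*

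**What the plan says.** The section on power analysis and sample size cites the team's meta-analysis, which found "beneficial effects ranging from small to large [17], with contributing studies including 10 to 67 participants". It then reports an a priori G*Power calculation for "comparing two intervention groups across three measurement intervals", applied to any of the primary outcomes. The target is introduced with "To detect a medium effect", followed by f² = .25, and the result is that "at an alpha of .05 and power of .90, 36 participants will need to be recruited". An attrition allowance follows: "To account for potential 20% attrition, 44 participants (i.e. 22 per group) will be targeted for recruitment".

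The section on data analysis names the test that carries the treatment comparison: "Each GLMM will be assessed for statistically significant Group x Time interaction effects".

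The article does not state the correlation between time points, the sphericity setting, or the effect as a difference in SD or score units.

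**The concern.** The symbol and the sample size do not belong together. An f² of .25 is a large effect that would need far fewer than 36 participants in this design, whereas f = .25 is the value usually labelled medium. Anyone checking the calculation as printed will fail to reproduce it.

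The label raises a second problem. In a repeated-measures interaction, f is a root mean square of interaction effects over all group-by-time cells, so a given f corresponds to a larger group difference than the same label suggests for a simple two-group comparison. A reader who takes *medium* as a moderate difference between arms would think the trial has 90% power for it. If it does not, a non-significant interaction says less about moderate benefit than the power statement implies.

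**Working it through.** **Inputs from the article.** k = 2 groups, m = 3 time points, alpha .05, power .90, N = 36 (44 recruited), tested by the Group x Time interaction.

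**Assumptions, not in the article.** Correlation ρ between time points = .5 and sphericity, because these recover 36 at f = .25. Other values of ρ are shown in step 4.

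**Formula.** Noncentral F for the within-between interaction:
- noncentrality λ = f² × N × m / (1 − ρ)
- df1 = (k − 1)(m − 1) = 2
- df2 = (N − k)(m − 1) = 2(N − 2)

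**Step 1. Reproduce the plan's 36.** With f = .25 and N = 36, λ = .0625 × 36 × 3 / .5 = 13.5 and df2 = 68, so power = .906. At N = 34, λ = 12.75 and power = .888. The smallest even N reaching .90 is therefore 36.

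**Step 2. Use the effect as printed.** With f² = .25 (f = .50), N = 10 gives power .892 and N = 12 gives .949, so 12 participants suffice. At N = 36 power would exceed .999. On the f² scale the printed effect is .25 / .0625 = 4 times the one that fits the sample size.

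**Step 3. Convert f = .25 to SD units.** Let the group difference be 0 at T0 and d at T1 and T2, in units of the within-group SD. The mean difference over time is 2d/3. The interaction effects in the six cells are ±½ × (−2d/3, d/3, d/3), and their mean square is ¼ × (4d²/9 + d²/9 + d²/9) / 3 = d²/18. Hence f = d/√18 and d = .25 × √18 = 1.06 SD. If the difference builds up linearly (0, d/2, d), f = d/√24 and d = .25 × √24 = 1.22 SD at T2.

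**Step 4. Power at smaller differences.** For the (0, d, d) pattern, d = 0.5 gives f = .118 and d = 0.8 gives f = .189. With 36 completers:

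| ρ | Power at 0.5 SD | Power at 0.8 SD | Power at f = .25 (1.06 SD) |
|---|---|---|---|
| .2 | .21 | .47 | .72 |
| .3 | .23 | .52 | .78 |
| .5 | .31 | .68 | .91 |
| .7 | .49 | .89 | .99 |
| .8 | .67 | .98 | >.99 |

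If all 44 are retained, power at ρ = .5 is .37 for 0.5 SD and .77 for 0.8 SD.

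**Cross-check.** A 20,000-run simulation at ρ = .5 and N = 36 gave .308 at 0.5 SD and .906 at 1.06 SD. A two-sample t test on change from baseline at ρ = .5 gave .308 at 0.5 SD.

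**The case against.** **The 90% is correct for f = .25.** This stands. Alpha, power and N agree with one another once the superscript is removed, and neither 36 nor 44 changes. A reader might infer that the stated power is simply false. The figures do not support that: the printed symbol is wrong, and so is reading the label as a moderate group difference.

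**The plan never sets 0.5 SD as its target.** This also stands. *Medium* beside .25 is the conventional label for f. The figures at 0.5 and 0.8 SD show what the label does not mean; they do not show that the trial fails a goal it set itself.

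**It is tempting to say the trial can reliably detect only differences above one SD.** That goes too far. For the (0, d, d) pattern, the difference detectable with 90% power at ρ = .5 is 1.05 SD with 36 completers but 0.95 SD if all 44 stay. With 36 completers it is 0.81 SD at ρ = .7 and 0.66 SD at ρ = .8. A baseline-adjusted mean of the two follow-ups would also help: power at 0.5 SD is then .54 at ρ = .5 and .81 at ρ = .8. Even these stay below .90 for 0.5 SD.

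**The correlation could go either way.** A low value is plausible for speech, which is measured with hearing aids before implantation and with the processor afterwards. That reason does not carry over to the six repeated cognitive tests. A sensitivity range should therefore extend to both sides of .5.

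**Another routine also returns 36.** A one-tailed test of a single regression coefficient with f² = .25 gives N = 36 (power .902). It does not fit the two-group, three-interval design that the article describes, so the interaction reading remains likelier. It remains an inference about settings that the article does not print.

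**A condensed article may leave the correlation and sphericity to a fuller document.** Agreed, and their absence alone is no finding. They are needed here because the corrected figure cannot be checked without them.

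**No passage claims that a null result would exclude moderate benefit, and Bayes factors are planned.** Both are true. Bayes factors lessen the reliance on p values but add no power.

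**Conclusion.** The point holds as a correction to the power statement. The effect printed as f² = .25 does not fit the stated sample size for the described interaction test: it needs 12 participants, and 36 fits f = .25. On that reading the 90% power belongs to a post-baseline group difference of about 1.06 SD, or 1.22 SD at T2 under linear build-up. At ρ = .5, 36 completers give power of about .31 at 0.5 SD and .68 at 0.8 SD; at ρ = .7 these become .49 and .89.

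The reproduction of 36 rests on ρ = .5, sphericity and the interaction routine. The SD conversion adds the assumed pattern of differences over time. None of these is stated in the article; the first three are the settings that recover its own number. The documents do not support concluding that the sample size was miscalculated or must change.

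**What to change.** In the section on power analysis and sample size:

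1. Replace f² = .25 with f = .25, after confirming this against the saved G*Power settings.
2. State the assumed correlation between time points (.5, if confirmed) and the sphericity assumption.
3. Add that, under those assumptions, f = .25 corresponds to a between-group difference of about 1.06 SD at both T1 and T2, and that *medium* is the conventional label for f.
4. Give power with 36 completers at 0.5 and 0.8 SD over correlations on both sides of .5, for example .2 to .8, as in the table above.

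Keep 36 completers and the recruitment target of 44. The change is to wording only. Its one cost is a less favourable power statement.

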### Test procedure

Participants who meet the clinical criteria for a cochlear implant will be recruited into the study. Participants will complete audiometric testing and speech/sound perception assessment within the 12 months preceding surgery and complete the pre-intervention cognitive, mood, and quality of life assessment within 1 week prior to implant. Participants will have the option to complete the pre-intervention assessment in their home or at the Ear Science Institute Australia at a time that is most convenient to them. Following cochlear implant surgery and recovery, participants will attend their ‘switch-on’ appointment where they will be provided with the standardised auditory training material by their implant audiologist. Following ‘switch-on’ appointments, participants will be randomised to either the adaptive or non-adaptive CCT group and the lead researcher will schedule a time within the same week to visit participant homes to set up the CCT equipment. As the CCT platform, Brain HQ will be delivered via the internet to participant’s home computers and the lead researcher will spend time explaining and demonstrating how to use the platform. Participant adherence to the training will be automatically monitored by the program and remotely by the lead researcher. Participants will be sent regular text messages during the intervention as polite reminders to complete their CCT sessions. Following completion of the training, participants will complete audiometric testing and a post-intervention assessment of their speech/sound perception, cognition, mood, and quality of life. The same outcomes will also be measured at the 3-month follow-up assessment to provide evidence of long-term benefits of CCT.

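### A target of 44 covers about 18% attrition from the required 36, not the stated 20%; the effect on power is minor

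*Protocol article*

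**What the plan says.** The section on power analysis and sample size reports an a priori G*Power calculation of the "required sample size when comparing two intervention groups across three measurement intervals". The effect is described as medium and printed as f² = .25. The result is given "at an alpha of .05 and power of .90, 36 participants will need to be recruited". The allowance for loss follows at once: "To account for potential 20% attrition, 44 participants (i.e. 22 per group) will be targeted for recruitment". No inflation formula is given, and neither the correlation between repeated measurements nor a sphericity assumption is stated.

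The section on data analysis and statistical methods plans generalised linear mixed models, with the Group × Time interaction as the first effect examined.

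**The concern.** An attrition allowance should leave the required number once the stated share has been lost. If N are needed and a fraction d of those entered will be lost, the number to enter is N/(1 − d). Multiplying by (1 + d) instead takes the percentage of the required number rather than of the number entered, and always gives too few. The target of 44 looks like the second calculation.

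At stake is whether the published justification is true as written: at the attrition it names, the plan expects fewer than the 36 it says it needs. How far power falls is a separate question and has to be computed.

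**Working it through.** **Inputs from the article (power analysis and sample size).** Two groups, three assessments, alpha .05, power .90, required N = 36, attrition 20%, target 44 (22 per group).

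**Inputs assumed.** Correlation between repeated measurements rho = .5; sphericity (epsilon = 1). The value .25 is read as Cohen's f, although the article prints f², because that reading reproduces 36.

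**Step 1: reproduce the 36.** Repeated-measures ANOVA, within-between interaction:
- Noncentrality λ = f² × N × m/(1 − rho) = 0.0625 × 36 × 3/0.5 = 13.5
- Numerator df = (2 − 1)(3 − 1) = 2; denominator df = (36 − 2)(3 − 1) = 68
- Power = .906

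In steps of two participants, 36 is the smallest N to reach .90, so the article's figure is recovered.

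**Step 2: the attrition allowance.**
- Dividing by the retained share: 36/(1 − 0.20) = 45; 46 (23 per group) for equal groups
- Multiplying up: 36 × 1.20 = 43.2, rounded up to 44, which matches the article
- Expected completers from 44: 44 × 0.8 = 35.2
- Expected completers from 45 and 46: 36.0 and 36.8
- Attrition that 44 covers exactly: 1 − 36/44 = 18.2%

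**Step 3: what the shortfall costs**, same model as Step 1.

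| Completers | Power |
|---|---|
| 36 | .906 |
| 35.2 (expected from 44) | .899 |
| 35 | .897 |
| 34 (17 per group) | .888 |

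**Step 4: sensitivity to the assumed correlation.** The N needed for .90 is 50 at rho = .3, 36 at rho = .5 and 22 at rho = .7. A very small change in rho closes the gap: 35 completers give .903 at rho = .51, and 34 give .900 at rho = .52.

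**The case against.** The strongest reply is that this is rounding. The 36 is itself rounded up to an even number and carries power of .906. Power of .90 is reached at about 35.3 completers, so an expected 35.2 falls short by roughly 0.1 of a participant, and .897 prints as .90 at the article's precision. A gap of one or two participants is also far smaller than the range of 22 to 50 that follows from the unstated correlation. In addition, a mixed model does not need complete records: someone lost between the post-intervention and 3-month assessments still informs Group × Time, although someone lost before the post-intervention assessment adds little. All of this stands as an argument about size. It does not make the sentence correct, because 44 less 20% is still below 36.

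It is also fair to object that the article gives no formula. That 36 was multiplied by 1.2 is a plausible inference and no more.

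A reader might go further and infer that the same 20% must also absorb people lost between enrolment and randomisation, since the target is worded as recruitment while the test procedure section says that, after switch-on, "participants will be randomised to either the adaptive or non-adaptive CCT group". The article does not support this as an error. It equates the 44 with 22 per group, and groups exist only after allocation, so the natural reading is 44 allocated participants. The word recruited is used loosely: the required 36 are also to be recruited, and the randomisation section speaks of the first participant recruited as being randomised. Nothing states which losses the 20% is meant to cover, and no rate of loss before randomisation is given.

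**Conclusion.** The attrition statement is wrong as written, by simple arithmetic that needs no assumption: 44 allows for 18.2% attrition, and a 20% allowance calls for 45, or 46 with equal groups. The shortfall is one or two participants.

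The effect on power is minor: .897 to .899 with about 35 completers against the stated .90, a loss of less than one percentage point from .906 at the full 36. Those power figures rest on f = .25, rho = .5 and sphericity, of which the last two are assumed. A reader might infer that the trial is underpowered or that the stated .90 is materially missed. The documents do not support that: the gap disappears with a marginally higher correlation, and the planned model can recover part of what is lost. This is a minor correction to a published figure.

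**What to change.** Either of two changes settles it:

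- Keep the target and correct the percentage: state that 44 participants (22 per group) allow for about 18% attrition. This costs one sentence and no participants.
- Keep the 20% allowance and correct the target: state 45, or 46 (23 per group) for equal groups. This costs one or two more participants.

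The trial status section says that recruitment had not begun, so on the article's own account either change can be made before the first enrolment. No change to the design or the analysis follows from this point.
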